## Abstract

**Background:**

Despite large-scale efforts to diagnose people living with HIV, 54% remain undiagnosed in sub-Saharan Africa. The gap in knowledge of HIV status and uptake of follow-on services remains wide with much lower rates of HIV testing among men compared to women. Here, we design a study to investigate the effect on uptake of HIV testing and linkage into care or prevention of partner-delivered HIV self-testing alone or with an additional intervention among male partners of pregnant women.

**Methods:**

A phase II, adaptive, multi-arm, multi-stage cluster randomised trial, randomising antenatal clinic (ANC) days to six different trial arms. Pregnant women accessing ANC in urban Malawi for the first time will be recruited into either the standard of care (SOC) arm (invitation letter to the male partner offering HIV testing) or one of five intervention arms offering oral HIV self-test kits. Three of the five intervention arms will additionally offer the male partner a financial incentive (fixed or lottery amount) conditional on linkage after self-testing with one arm testing phone call reminders.

Assuming that 25% of male partners link to care or prevention in the SOC arm, six clinic days, with a harmonic mean of 21 eligible participants, per arm will provide 80% power to detect a 0.15 absolute difference in the primary outcome. Cluster proportions will be analysed by a cluster summaries approach with adjustment for clustering and multiplicity.

**Discussion:**

This trial applies adaptive methods which are novel and efficient designs. The methodology and lessons learned here will be important as proof of concept of how to design and conduct similar studies in the future. Although small, this trial will potentially present good evidence on the type of effective interventions for improving linkage into ART or prevention. The trial results will also have important policy implications on how to implement HIVST targeting male partners of pregnant women who are accessing ANC for the first time while paying particular attention to safety concerns. Contamination may occur if women in the intervention arms share their self-test kits with women in the SOC arm.

**Trial registration:**

ISRCTN, ID: 18421340. Registered on 31 March 2016.

**Electronic supplementary material:**

The online version of this article (doi:10.1186/s13063-017-2093-2) contains supplementary material, which is available to authorized users.

## Background

Sub-Saharan Africa (SSA) accounts for 70% of the global HIV burden despite rapid scale up of HIV services including testing [1]. Analysis of the HIV care cascade indicates a striking fall-off in numbers between testing and linkage into HIV care or prevention [2]. Men regularly feature among populations with lower uptake of HIV testing across SSA [3] and lower rates of linkage into care or prevention [4] in the era of extremely ambitious targets for HIV [5]. The 90-90-90 targets aim to diagnose 90% of all HIV cases, start 90% of diagnosed HIV cases on treatment, and achieve viral suppression in 90% of those started on HIV treatment [5]. Awareness of HIV status among male partners of antenatal clinic (ANC) women attendees is low with less than 35% undergoing HIV testing when invited through their partner [6]. African women face substantial risk of acquiring HIV infection, estimated at 3.6% per pregnancy in study cohorts [7]. Over 90% of pregnant women access ANC services, providing an ideal opportunity to reach both partners with HIV testing and counselling services (HTS) [8].

A number of strategies have been found to increase uptake of HIV testing among male partners of ANC attendees, including home-based testing [9, 10], provider-initiated testing and counselling (PITC) [11], couples testing during antenatal visits [12] and home-based couple or partner testing [13, 14]. Key limitations of these strategies include: logistical difficulties of wide-scale implementation where home visits are required, lack of convenience, costs, lack of confidentiality and failure to prioritise men’s own health [15–17]. HIV self-testing (HIVST) is an alternative approach with the potential to increase couple or partner testing [18] and has been found to be highly acceptable to men in Malawi [19, 20]. Here, we define *HIVST-plus* as offering HIV self-testing along with an additional intervention aimed at improving linkage into HIV care or prevention. Such additional interventions include facilitated linkage [21], financial incentives (FI) [22] and short messaging services (SMS) [23].

This wide range of interventions presents technical challenges related to appropriate study design and analysis methods in order to identify optimal strategies [24]. Such complexity can be handled by applying multi-arm, multi-stage (MAMS) designs, which are more flexible by allowing pre-specified adaptations at interim analysis, as well as more efficient with respect to time and cost than standard parallel designs [25, 26]. In MAMS designs, several interventions are included in the first stage of the trial with pre-specified adaptations at interim analysis. Such a trial may either be a multi-stage phase II or III trial, or can be done as a seamless trial combining all the three trial phases separated by interim analyses [27]. In general, MAMS designs involve comparing each of several interventions to a control arm using interim analysis [25], providing an unbiased approach to investigating and selecting multiple phase II candidates under consideration for a future phase III trial [26]. Although predominantly used in the pharmaceutical industry to date, MAMS trial designs could have value in public health evaluations where randomising at the cluster level is often preferred. Furthermore, public health interventions are often complex involving multiple components and understanding the effect of each component may help inform the optimal choice [28].

Here, we describe the design of a phase II, adaptive, MAMS cluster randomised trial (CRT) with clinic day (not individual women) as the unit of randomisation. Our primary objective is to identify leading candidate interventions based on HIVST for improving HIV testing and linkage into care or prevention for male partners of ANC attendees in Blantyre, Malawi.

## Methods

### Design

This is a phase II, adaptive, MAMS CRT using ANC day as the unit of randomisation. As a phase II trial the study is intended to investigate *efficacy* relating to uptake of testing and subsequent HIV services by the male partner, *safety outcomes, and* to provide an estimate of *acceptability* to the pregnant woman. The trial will have one interim analysis during which pre-planned adaptations will be made as described below, followed by final analysis at the end of the second stage (two-stage MAMS design). The first stage will have six arms with one SOC and five intervention arms (Fig. 1). At the end of the first stage, a 3-point criteria will be considered by an independent Data Safety and Monitoring Board in order to drop intervention arms. Each intervention versus the SOC yielding *p* > 0.2 will be considered to be dropped; safety concerns; and costs will guide recommendations to drop or retain an intervention arm at the end of the first stage. The trial will not stop for efficacy at the interim analysis.

**Fig. 1 Fig1:**
[figure not shown]
Schema of the phase II, adaptive, multi-arm, multi-stage cluster randomised trial. A two-stage, multi-arm, multi-stage (MAMS) trial design starting with six arms in the first stage. At interim analysis (end of first stage) some trial arms may be dropped, with recruitment to the remaining arms aiming to narrow down to a few arms that may be carried forward to a definitive (phase III) trial

Analysis of second stage (end of trial) data will potentially lead to a definitive study (phase III) involving arms that show promise at the end of the second stage. A sample size of 36 ANC days (six per arm) will be required for the first stage (see the ‘Sample size considerations’ section below for justification). In order to control the family wise error rate (FWER) at the specified significance level (*α* = 0.2) for the five comparisons with the SOC arm, Dunnett’s test [29] will be applied.

### Trial simulation

A simulation study was set up to compute the overall probability of the trial to find at least one intervention whose efficacy is different compared to the SOC arm at the end of stage 2 (minimal power). The simulation was conducted under the alternative hypothesis with an assumed effect of 29–40% versus 25% in the SOC arm (Table 1). Additional key assumptions included that each ANC day (cluster) would have 20 participants with power set at 80% for each stage (Table 1). The simulation showed that at least two interventions would significantly improve the trial primary outcome (Table 2). These interventions would then be further tested in a potential phase III trial.

**Table 1 Tab1:** Simulation inputs

Description	Input
Number of ANC days (clusters) per arm for both stages	6–20
Number of participants per ANC day	20
Linkage to care or prevention for the SOC arm in stages 1 and 2	25%
Linkage to care or prevention for the 5 intervention arms in stages 1 and 2	29–40%
SD of the mean of cluster-level proportions per arm (7 clusters, stage 1)^a^	0.05–0.08

*ANC* antenatal care, *SOC* standard of care, *SD* standard deviation

^a^Computed using *σ* = *k* × *μ* where *σ* is the standard deviation of the true cluster-level proportions; *k* is the coefficient of variation (assumed to be 0.2) and *μ* is the mean of the proportions per arm

Operating characteristics: stage 1 *α* = 0.2; stage 2 *α* = 0.1; 1 − *β* = 0.8

**Table 2 Tab2:** Simulation results

	First stage		Simulations in which arm was dropped at interim^c^	Assumed
Study arm	^a^Proportion	SD^b^	Proportion	Proportion^d^
1 Standard of care	0.250	0.048	NA	0.250
2 Intervention	0.291	0.055	0.441	0.290
3 Intervention	0.299	0.058	0.336	0.300
4 Intervention	0.310	0.059	0.215	0.310
5 Intervention	0.321	0.061	0.114	0.320
6 Intervention	0.400	0.078	0.000	0.400

Exact intervention not specified here as there is no evidence about a particular one of the 5 interventions being investigated

*SD* standard deviation

^a^Proportion of male partners linked to care or prevention

^b^Assumed (0.050, 0.058, 0.060, 0.062, 0.064, 0.080) in arms 1–6, respectively

^c^Scenarios assumed for the 6 trial arms at the start

^d^If *p* value was > 0.2 at interim analysis, discontinued from recruitment

### Study setting and population

The study will recruit participants from Ndirande, Zingwangwa and Bangwe primary health centres (PHC) in urban Blantyre, Malawi. All women attending for antenatal care for the first time at these PHCs and their male partners will be eligible for participation (see Additional file 1). Women and their male partners will be excluded if they received couple or partner HIV testing in the current pregnancy; if either are aged below 18 years of age; if the male partner is reported to be HIV positive by the pregnant woman; if already recruited in this trial; and if not urban Blantyre resident. Malawi has recently (September 2016) implemented the test and treat approach where everyone diagnosed with HIV starts antiretroviral treatment (ART) immediately.

### Randomisation and recruitment flow

Each ANC day was randomised to any one of the six trial arms using a randomised permuted block design in a ratio of 1:1:1:1:1:1 (Fig. 2). All three PHCs are of comparable size and serving comparable catchment populations, and, therefore, stratification was not deemed necessary. The allocation sequence was generated by an independent statistician using computer-generated random numbers [30]. The file containing the complete randomisation sequence will only be accessible to the independent statistician.

**Fig. 2 Fig2:**
[figure not shown]
Randomisation, recruitment, and outcome evaluation. Each cluster (antenatal clinic day) is randomised to any of the six trial arms. All women attending their first antenatal clinic are briefed about the general purpose of the trial without receiving trial arm-specific information. Women then undergo one-on-one eligibility screen and arm-specific information. Women who are eligible and accept to participate are then given a male partner invitation letter alone or with two self-test kits to take home

Field workers will enrol women into one of the six study arms on the morning of each ANC day after receiving the randomisation allocation for that ANC day (see Additional file 1). Women will receive study information in a group while in the ANC waiting area followed by one-on-one eligibility assessment and subsequent recruitment. Study information given during group sessions will not reveal details of arm-specific procedures to avoid potential non-participation associated with knowledge of procedures for each arm. All women who show interest at this stage will provide unwritten consent to participate by show of hands followed by written or witnessed thumb-print consent.

### Standard of care arm (SOC)

In the SOC arm women will receive a personalised letter only addressed to their male partner inviting him to go to the male-friendly clinic (MFC) to have an HIV test, receive HIV care or prevention and pregnancy-related education. The MFC is being implemented by the trial, and will offer men attending confirmatory HIV testing, facilitate linkage to HIV care or voluntary male medical circumcision (VMMC), and pregnancy-related health education.

### Intervention arms

In all five intervention arms, the woman will receive self-test instructions and two self-test kits to take home. The test kits, test instructions and a personalised letter will be delivered to the male partner by the woman in order to initiate dialogue for him to test and link to the MFC for HIV care or prevention as appropriate.

The five intervention arms differ with respect to financial incentives, participation in a lottery, and phone call reminders received by the male partner. Women in the first intervention arm will only receive the letter and the two self-test kits. In the two fixed financial incentive (FI) arms, male partners who self-test (test) and link into the MFC will receive an equivalent of US$3 or US$10 in the low- and high-FI arms, respectively. In the lottery FI arm, male partners who test and link into the MFC will have a 10% chance of winning US$30. In the final intervention arm, male partners will receive a phone call, through a number given to the study team by the woman at enrolment, to remind him to test and link into the MFC. All FIs will be disbursed as cash through mobile money in the trial in order to safeguard the safety of staff and are conditional on the male partner linking into the MFC.

### Primary and secondary outcomes

The primary outcome is the proportion of male partners of ANC attendees who test for HIV and link into HIV care or prevention within 28 days of enrolling the woman (Fig. 3). Thus, the primary outcome is defined as presentation of the male partner at the MFC with a used self-test kit (if in the intervention arm) or undergoing spot HIV testing with a study HIV counsellor within 28 days AND being referred for HIV care if HIV positive or VMMC if HIV negative and uncircumcised. There are four secondary outcomes: the proportion of male partners who test for HIV within 28 days (as reported by the woman); the proportion of women who accept to participate in their allocated trial arm; risk of serious adverse events (SAEs) in men and women in the study; and the total cost of implementing each trial arm. All outcomes will be analysed at cluster level (see the ‘Statistical analysis’ section).

**Fig. 3 Fig3:**
[figure not shown]
Schedule of enrolment, interventions and assessments (Standard Protocol Items: Recommendations for Interventional Trials (SPIRIT))

### Outcome measurement

All male partners who present at the MFC in the SOC arm will be offered a single finger-prick HIV test with Determine 1/2™ as per Malawi national testing algorithm. An HTS counsellor will re-read a used self-test kit if the participant returns one as evidence of self-testing in the intervention arms. Participants who return with unused self-test kits or without self-test kits will be requested to self-test in the presence of the counsellor. All HIV results will be recorded on a data form followed by confirmation of HIV-positive results in parallel using Determine 1/2™ and Uni-Gold, with facilitated linkage to HIV care. All men who test HIV negative and report to be uncircumcised will be offered VMMC to be conducted by Population Services Internal (PSI). Thus, measurement of primary outcome includes evidence of an HIV test, confirmatory testing, and referral to HIV care or VMMC as appropriate within 28 days of the woman being recruited.

The secondary outcome of HIV testing among male partners will also be measured though proxy reporting by the woman using audio computer-assisted self-interview (ACASI) during her next ANC visit 4 weeks later. Participation in the allocated trial arm will be measured by computing the proportion of women who accept to participate after receiving trial-arm-specific information using the denominator of the total number of women who are eligible. All women will be asked to report any adverse events through ACASI at their next ANC visit while men who present to the MFC will be asked to report any adverse events. A costing tool validated in urban Blantyre [31] will be used to capture the costs associated with providing the service in each trial arm. The cost and outcome data will be used to estimate the cost per male partner tested for HIV, and cost per HIV-positive male identified through all SOC and intervention arms.

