The trial results will also have important policy implications on how to implement HIVST targeting male partners of pregnant women who are accessing ANC for the first time while paying particular attention to safety concerns. In a recent cohort study where HIV-negative pregnant women collected three oral self-test kits in Kenya 51% reported that their male partners had self-tested with none of the women reporting any SAEs [40]. Unlike in the Kenya study, where only HIV-negative pregnant women were eligible, this trial will recruit pregnant women, regardless of HIV status, who are attending their first ANC. The group of women recruited here receive the offer of an HIV test routinely making this trial design readily scalable. Measuring actual HIV testing is extremely difficult with HIVST as by definition disclosure depends on the individual. Our HIV testing outcome will be measured objectively through observed returned used/unused self-test kits by the man and also proxy reporting by the woman which minimises information bias.

A major anticipated constraint is potential for SAEs resulting mainly from intimate partner violence (IPV) to women, although evidence from studies using other populations and other HTS models suggests that this approach is unlikely to increase this problem [6]. A recent large HIV self-testing study in Malawi found no increase in IPV, despite an active community liaison system among 27,000 self-testing participants [20]. We will carefully monitor IPV, and have deliberately listed this as a secondary (safety) outcome. Although it will not be possible for participants and recruiting staff to predict the next-day recruiting arm, the knowledge of FI arms may result in altered decision-making about health care seeking. For example, a woman may choose to postpone her ANC attendance in the hope of being recruited in a FI arm, or indeed want to switch between arms.

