There is potential for contamination if women in the intervention arms share their self-test kits with women in the SOC arm. In order to minimise this problem, we will ask women and their male partners in the intervention arms to bring used or unused self-test kits at follow-up and when they link into the MFC, respectively. We will also attempt to measure the magnitude of this problem by asking all women and male partners who link into the MFC in the SOC arm if they received self-test kits. There is potential bias in the estimation of the treatment effect and confidence intervals due to interim selection process of potential effective interventions which we will not explore.

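### A used kit brought in by the man counts as his own HIV test only in the intervention arms, so a non-reactive kit used by someone else can bias the primary comparison in their favour; the size is unknown and may be small

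*Protocol article*

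**What the plan says.** All references are to the Protocol article.

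- **Primary and secondary outcomes.** The outcome is that the man tests and links within 28 days. In the operational definition, the test component is met by "presentation of the male partner at the MFC with a used self-test kit (if in the intervention arm) or undergoing spot HIV testing". The spot test is done by a counsellor of the trial. Referral for care or circumcision, as applicable, is also required.
- **Intervention arms.** "In all five intervention arms, the woman will receive self-test instructions and two self-test kits to take home".
- **Outcome measurement, intervention arms.** "An HTS counsellor will re-read a used self-test kit if the participant returns one as evidence of self-testing in the intervention arms". Otherwise: "Participants who return with unused self-test kits or without self-test kits will be requested to self-test in the presence of the counsellor". Only HIV-positive results are followed by confirmatory testing.
- **Outcome measurement, SOC arm.** "All male partners who present at the MFC in the SOC arm will be offered a single finger-prick HIV test".
- **Discussion.** The authors write: "Our HIV testing outcome will be measured objectively through observed returned used/unused self-test kits by the man", alongside the woman's proxy report. They ask for used and unused kits to be brought back, in order to limit sharing with women in the SOC arm.

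**The concern.** The outcome is about this man's test, but the evidence for it differs by arm. An on-site test shows that he was tested. A used kit shows that somebody was. With two kits in the household, the one he carries in may have been used by his partner or another person. If it is non-reactive, the stated procedure does not test him.

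SOC men have no such route, so any error it causes adds successes to the intervention arms alone. The stage 1 comparison with SOC is the first of the three criteria for dropping arms, and its threshold is a deliberately lenient 0.2. Even a modest one-directional error could help an arm stay in.

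**Working it through.** **1. Evidence for the test component, by type of attender**

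| Attender at the male-friendly clinic | What meets the test component | Is the man himself tested there? |
|---|---|---|
| SOC | Finger-prick test | Yes |
| Intervention, unused kit or no kit | Self-test in front of the counsellor | Yes |
| Intervention, used reactive kit | Kit re-read, then confirmatory tests | Yes |
| Intervention, used non-reactive kit | Kit re-read | No test is stated |

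Only the last row is exposed, and it exists only in the intervention arms. This follows from the outcome definition as written, not merely from the article's silence on kit labels.

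**2. Who adds a false success**

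A man who arrives with another person's kit but would have accepted an on-site test would have met the test component anyway. The count is inflated only by men who would have declined that test, or who attend because a kit spares them one. Attendance within 28 days is still required of everyone.

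**3. The plan's own figure**

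Inputs from Sample size considerations: p0 = 0.25, p1 = 0.40, m = 21 per clinic day, k = 0.10, power 0.80. Significance level 0.2 is taken as two-sided and pair-wise; sidedness is not stated.

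- V = p0(1−p0)/m + p1(1−p1)/m + k²(p0² + p1²) = 0.00893 + 0.01143 + 0.00223 = 0.02258
- c = 1 + (1.2816 + 0.8416)² × V / 0.15² = 1 + 4.508 × 0.02258 / 0.0225 = 5.52, rounded up to 6

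The stated six clinic days per arm is reproduced, so the same formula can be used for illustration.

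**4. Illustration with no true effect**

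Let the intervention arm gain e points of false success over a true 25% (e is an assumption). With six days per arm, the chance of a result favouring the intervention is Φ(e × √(5/V) − z), where V is recalculated at p1 = 0.25 + e. For unadjusted two-sided p<0.2, z = 1.2816. The plan compares Dunnett-corrected p values with 0.2. For five comparisons, a normal approximation by simulation gives z = 1.916, two-sided.

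| e (points) | Apparent risk ratio | e√(5/V) | Pair-wise p<0.2 | Dunnett-type threshold |
|---|---|---|---|---|
| 0 | 1.00 | 0 | 0.10 | 0.03 |
| 1 | 1.04 | 0.161 | 0.13 | 0.04 |
| 2 | 1.08 | 0.319 | 0.17 | 0.06 |
| 3 | 1.12 | 0.475 | 0.21 | 0.07 |
| 5 | 1.20 | 0.782 | 0.31 | 0.13 |

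**5. Illustration at the design effect**

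If the counted proportion is 40% and a share q of those successes lacks the man's own test, the true proportion is 0.40(1−q). For q = 2%, 5%, 10% and 20% this is 39.2%, 38%, 36% and 32%. The true risk ratio is then 1.57, 1.52, 1.44 and 1.28, instead of 1.60.

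**The case against.** **What stands**

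- Much could be in documents not shown. Kit labels, a counsellor's question about who used the kit and the wording of the woman's questionnaire normally sit in the full protocol. Their absence from an article is no fault. The point rests only on the stated definition, under which a used kit is sufficient.
- There are partial checks. Kits are to be brought back, and the woman reports by computer-assisted interview whether her partner tested. The article does not link that report to the primary outcome. The authors also acknowledge that actual testing is very hard to measure with self-testing.
- Effects on arm selection need not all run one way. A missed positive result lowers the number of HIV-positive men found. That raises the cost per positive in the intervention arms, which counts against them at the interim.
- 32 of the 36 stage 1 clusters were already covered at submission (Trial status). Redefining the outcome now would make ascertainment differ between two stages whose p values and log risk ratios are to be combined.
- This is a phase II screen that openly tolerates carrying an ineffective arm forward.

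**Stronger readings that the documents do not support**

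- *That nothing ties any used kit to the man.* A reactive kit leads to confirmatory testing of him.
- *That the plan expects kits to circulate freely.* The Discussion says: "There is potential for contamination if women in the intervention arms share their self-test kits with women in the SOC arm". That concerns SOC women. A kit passed to another household is less available for this man to return.
- *That the incentives reward bringing a used kit.* Payment is for testing and linking. A man tested on site meets that condition too, and nothing pays more for a kit.
- *That a large part of the 15-point target difference could be spurious.* Such a figure needs three assumed rates: the share qualifying on a kit, the share of kits not the man's own, and the share who would refuse the on-site test. The documents give none of them.

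**Conclusion.** The concern holds in limited form. The stated outcome definition opens a false-success route, through non-reactive kits used by someone else, in the intervention arms only. Through this route the comparison with SOC can be biased in their favour.

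The size is unknown and may be small. The 1 to 5 points used above are assumed values, chosen to show sensitivity. At those values the pair-wise chance of a favourable stage 1 p<0.2 under no effect goes from 0.10 to 0.13–0.31. Against a Dunnett-type threshold it goes from 0.03 to 0.04–0.13. Both rest on a normal approximation with the design's m and k.

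This does not show that the trial's comparisons are invalid. It does mean that the Discussion's claim of objective measurement is too strong, and that the extent of the problem should be made measurable.

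**What to change.** Keep the primary definition the same in both stages, and collect what is needed to judge it.

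1. **From stage 2, mark both kits** with the participant ID and show which one is the male partner's.
2. **At the clinic, record for each success** whether it rests on an observed test or on a used kit. If on a kit, record which one and his statement that he used it.
3. **Add an item to the woman's 4-week interview** asking who used each kit.
4. **Pre-specify two sensitivity analyses, reported by arm.**
   - (a) Attendance at the clinic within 28 days whatever the test evidence, applied identically in all arms. This removes the difference in evidence, but not any extra attendance that a kit itself prompts. It needs attenders who declined a test to have been recorded.
   - (b) Used-kit successes counted as not tested where the woman's report says he did not test. In stage 1, use the existing report of whether he tested. This can remove successes only in the intervention arms, so read it beside (a), and state how missing reports are handled.
5. **Report primary successes by type of evidence** in each arm.
6. **In the Discussion**, replace the claim of objective measurement with a statement that a used kit shows that someone tested.

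The cost is labels, a form field, one or two interview items and two analyses, with no extra staff or participants. Labels reduce substitution but do not remove it, and stage 1 kits cannot be labelled retrospectively.
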